### Recruitment and retention

Enrolment started at Khayelitsha District Hospital on 22 July 2022. We aim to enrol 275 mother-infant dyads by the end of 2023. Informed consent is requested to conduct an enrolment maternal interview; four in-person follow-up visits at weeks 2, 6, 10, and 24 post-randomization; child hospitalization medical record review; and child height and weight measurements (Table 1). Eligible mothers are consented to the study by a research assistant in the mother’s language of her choice. Mothers are informed of the risk of loss of confidentiality and the need to access medical records. Mothers sign the informed consent form in a private space at the hospital. The research assistant conducts an enrolment maternal interview and completes a baseline questionnaire. The study provides transport to and from the study follow-up research site; mothers receive a R180 (~ US $10) voucher at each study visit, for their participation time and any other study-related costs. A participant who considers withdrawing from the study is informed about modified follow-up options (telephone interviews). If a participant withdraws from the study, we confirm if the participant agrees to medical and laboratory records access in line with the original consent. For a participant who fails to return for a study visit, the research team attempts to contact the participant and reschedule the missed visit. Before a participant is deemed lost to follow-up, efforts to regain contact with the participant continue through telephone calls or home visits.

**Table 1 Tab1:** Time schedule of enrolment, interventions, assessments, and visits for participants

	**Recruitment**	**Visit1**	**Visit 2**	**Visit 3**	**Visit 4**	**Study completion form**
**Target**	At delivery	2 weeks	6 weeks	10 weeks	24 weeks	To be completed when the participant is LTFU, withdraws from the study, or at the end of the study
**Window**	Within 24 h of giving birth	± 4 days	± 7 days	± 14 days	± 14 days	
**Screening for eligibility**	x					
**Detailed informed consent**	x					
**Randomization**	x					
**Visit preparation, follow-up, and tracking of participants**						
Telephonic reminder of a visit		x	x	x	x	
Schedule next visit and complete appointment card	x	x	x	x		
**Interventions**						
Intervention group: text messaging weekly for 24 weeks						
Intervention group: motivational interview		x	x	x		
Usual care group: referred for usual care if necessary		x	x	x		
**Assessment**						
Demographics	x					
Baseline data	x					
Anthropometrics		x	x	x	x	
Maternal NHLS antenatal CD4 count and viral load	x					
NHLS infant HIV-PCR result				x	x	
Infant feeding questionnaire		x	x	x	x	
Health questionnaire including medications (e.g. immunization, morbidity and mortality, infant weight, and height measurements)		x	x	x	x	
Health record reviews—hospital electronic administration systems: infant hospitalization and mortality					x	

### Sequence generation and allocation concealment mechanism

The principal investigator used Stata 17 random number generating command (RALLOC), to generate the fixed randomization allocation sequence using permuted block sizes of 2, 4, and 6. Participants are enrolled by the research assistant. Baseline data are captured using the Research Electronic Data Capture (REDCap) mobile application and uploaded to the REDCap database. The principal investigator assigns a study group sequentially, using the allocation table that is locked, unmodifiable and stored in the REDCap database.

### Blinding

A research assistant not administering the study interventions completes study questionnaires at follow-up visits, without knowledge of the study assignment. A research assistant administering the study interventions is not blinded to the study assignment. The independent data analyst performs unblinded analyses. Study participants are aware of the assigned study group.

### Study procedures and measurements

Baseline sociodemographic and clinical characteristics are obtained by interviewing the mother and abstracting medical records data. Following enrolment at Khayelitsha District Hospital, participants have in-person follow-up visits at Masiphuhlisane Research Centre. At each visit, a research assistant interviews the mother using a questionnaire of food items given to the baby in the last week or 24 h preceding the inquiry. The infant feeding questionnaire was developed using the World Health Organization standardized instrument [30]. Infant death, hospitalization, and safety events are identified by interviewing the mother. Infant weight and height are measured at each visit. Participants who fail to attend a visit are interviewed telephonically. See the study participant flow diagram in Fig. 1.

**Fig. 1 Fig1:**
[figure not shown]
Study participant flow diagram: schedule of enrolment, interventions, and assessments

### Data management

Data are entered remotely using password-protected tablets and stored electronically on password-protected REDCap database hosted at Stellenbosch University institutional servers. The principal investigator (PI) manages the REDCap database access. Research assistants are granted permission for data entry. The data analyst has permission to view the database and will only receive anonymized de-identified datasets at the time of analysis. The PI reviews data quality and can make edits to the database. Study documents, including signed informed consent forms, are filed in a lockable cabinet at study sites. After database lock, all electronic case report forms are archived for 15 years. The data will be deposited into the SUNScholarData, a data repository that is managed by the Stellenbosch University Library.

### Statistical methods

The participant is the unit of reporting. The interim analysis includes the first 138 mother-infant pairs enrolled (half of the total enrolment). Table 2 provides a summary of methods of analysis for each endpoint. An independent data analyst performs data analysis during trial monitoring. The data analyst writes a statistical code that includes the population used in a table or figure that is explicitly set at the start of a block of code that computes the output; at the start of any code, a set of comments give references to inputs and outputs. The Stata software package is used for analysis.

**Table 2 Tab2:** Endpoints, hypothesis, and methods of analysis

Endpoint measure	Hypothesis	Method of analysis
Primary 1: exclusive breastfeeding at 6 months of child age	Text messaging and motivational interviewing lead to higher rates of exclusive breastfeeding than usual care	▪ Standard proportions test ▪ Binomial regression
Primary 2: any form of breastfeeding at 6 months of child age	Text messaging and motivational interviewing lead to higher rates of any form of breastfeeding than usual care	▪ Standard proportions test ▪ Binomial regression
Exploratory analysis of primary endpoint: time to stopping breastfeeding	Text messaging and motivational interviewing lead to a higher median time to stopping breastfeeding than usual care	▪ Kaplan–Meier survival analysis ▪ Cox proportional-hazards regression model
Secondary 1: number of all-cause infant hospitalization and death as a composite endpoint Time to first all-cause death or hospitalization	Text messaging and motivational interviewing lead to a reduction in the number of all-cause hospitalizations or all-cause deaths than usual care	▪ Mean cumulative function ▪ Poisson random-effects model ▪ Kaplan–Meier survival analysis ▪ Cox proportional-hazards model
Secondary 2: infant growth	Text messaging and motivational interviewing lead to improved infant growth than usual care	▪ Mixed linear regression models

### Primary efficacy confirmatory analysis

A group-sequential standard proportion test using the O’Brien-Fleming boundaries rejects the null hypothesis of no difference in exclusive breastfeeding rates between the intervention and usual care groups, at the end of the study if the computed *z*-statistic exceeds the prespecified stopping boundary value of 1.9776.

### Exploratory efficacy analyses of primary endpoints

The potential confounding effect of baseline sociodemographic and clinical variables is adjusted for in the binomial regression, Cox proportional hazards, mixed linear regression, and Poisson regression models.

#### Dichotomous endpoints

To determine whether text messaging plus motivational interviewing leads to higher rates of (i) exclusive breastfeeding or (ii) any form of breastfeeding than usual care, the relative risk (by binomial regression) of exclusive breastfeeding or any form of breastfeeding is computed for the study group.

#### Time to event endpoints

Analysis of time to stopping breastfeeding is presented by Kaplan–Meier survival curves separately by study group and comparisons are made with the log-rank test. Participants are censored at 24 weeks or the last completed visit. A Cox proportional hazard regression analysis on the study group, with stopping breastfeeding as the endpoint, using the age of child at the time of stopping breastfeeding as the time at risk of the hazard of stopping breastfeeding is compared to binomial regression for consistency of associations.

### Exploratory efficacy analyses of secondary endpoints

#### Time to event endpoints

Time to first all-cause death or hospitalization is analysed using Kaplan–Meier survival curves and Cox proportional-hazards model. Time from birth to occurrence of first hospitalization or death is used as time at risk for the survival analysis.

#### Continuous endpoints

The evolution of weight-for-age, length-for-age, and weight-for-length *z*-scores (World Health Organization standardized) is compared between the study groups using mixed linear regression models.

#### Count outcomes

A Poisson random-effects model is used to compare counts of all-cause infant hospitalization, death, and non-routine sick clinic visits between the study groups, allowing for a lack of statistical independence resulting from the observation of multiple events in some infants. Results are adjusted for calendar time to account for infant health progression, leading to a decreasing incidence of events among infants over time.

The number of all-cause infant hospitalization, death, and non-routine or sick clinic visits (composite endpoint) is compared between the study groups using the mean cumulative function. The intensity rate is reported.

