## Objectives and hypotheses

The trial is primarily evaluating the effects of a combined intervention of interactive weekly mobile phone text messaging plus motivational interviewing in promoting (a) exclusive breastfeeding and (b) any form of breastfeeding, until 6 months of child age, compared to usual care, among mothers living with HIV. Secondarily, to compare the effects of the combined intervention in improving infant health outcomes, including (a) reduction in all-cause hospitalization and mortality rates and (b) improvement in infant linear growth, compared to usual care, among HIV-exposed infants aged 0–6 months. We hypothesize that breastfeeding will be sustained among mothers living with HIV receiving the combined intervention and that this will contribute to improved infant health outcomes.

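### The mean cumulative function for secondary endpoint 1 counts sick-clinic visits on top of the hospitalisations and deaths that define the endpoint; a lesser point is that its calendar-time adjustment is justified by an infant-age effect

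*Protocol article*

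**What the plan says.** Table 2 (Statistical methods) lists "Secondary 1: number of all-cause infant hospitalization and death as a composite endpoint". Its hypothesis is that the intervention will "lead to a reduction in the number of all-cause hospitalizations or all-cause deaths than usual care". Four methods are assigned: mean cumulative function, Poisson random-effects model, Kaplan–Meier and Cox. The secondary aim in Objectives and hypotheses has the same scope, "reduction in all-cause hospitalization and mortality rates", as does the abstract.

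The survival part keeps to that scope and runs from birth: "Time from birth to occurrence of first hospitalization or death is used as time at risk for the survival analysis" (Exploratory efficacy analyses of secondary endpoints, Time to event endpoints).

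The Count outcomes section differs. For the Poisson model it says: "A Poisson random-effects model is used to compare counts of all-cause infant hospitalization, death, and non-routine sick clinic visits between the study groups". For the mean cumulative function it says: "The number of all-cause infant hospitalization, death, and non-routine or sick clinic visits (composite endpoint) is compared between the study groups". On the time adjustment it says: "Results are adjusted for calendar time to account for infant health progression, leading to a decreasing incidence of events among infants over time".

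Sick-clinic visits appear under Endpoint variables as a mother-reported item, but not as an endpoint in Table 2. The sample size section calls the secondary analyses exploratory and says the trial is not powered for them.

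**The concern.** One named endpoint has two event sets. An analyst who follows Table 2 counts hospitalisations and deaths. An analyst who follows the Count outcomes section adds sick-clinic visits, at least for the mean cumulative function. Both follow the article, and both would report the result as secondary endpoint 1. The choice between them should not be open once the data are seen.

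The added component is also different in kind. A sick-clinic visit depends on the mother's decision to seek care as well as on illness. The intervention arm gets a weekly text and a call after a reported problem or no reply, and this contact could change care-seeking or its reporting without changing severe morbidity. Table 1 schedules a hospital record review at 24 weeks for hospitalisation and mortality, but lists none for clinic visits. A shift in the wider composite, or the lack of one, therefore cannot be read as the effect named in the objective.

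On the time term, a fall in event rates as infants develop is a function of age. Births are spread over the accrual period, so infants of different ages are at risk on the same calendar date. A calendar term does not, in general, remove an age trend.

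**Working it through.** **1. Event sets side by side**

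| Place | Method | Events |
|---|---|---|
| Objectives and hypotheses; abstract | – | hospitalisation, death |
| Table 2, secondary 1 | mean cumulative function, Poisson, Kaplan–Meier, Cox | hospitalisation, death |
| Time to event endpoints (secondary) | Kaplan–Meier, Cox | hospitalisation, death |
| Count outcomes | mean cumulative function | hospitalisation, death, sick-clinic visits, as one composite |
| Count outcomes | Poisson | the same three types; pooled or separate not clear |

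The article states no rate, event count or power for this endpoint, so there is no figure to reproduce.

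**2. Illustration of dilution (all inputs assumed)**

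Let *p* be the control-arm share of hospitalisations and deaths among all counted events. The composite rate ratio is *p* × RR(hospitalisation/death) + (1 − *p*) × RR(sick visits). With RR(hospitalisation/death) = 0.60:

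| *p* | RR(sick) = 1.0 | RR(sick) = 0.9 | RR(sick) = 1.1 |
|---|---|---|---|
| 0.10 | 0.96 | 0.87 | 1.05 |
| 0.20 | 0.92 | 0.84 | 1.00 |
| 0.30 | 0.88 | 0.81 | 0.95 |
| 0.50 | 0.80 | 0.75 | 0.85 |

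The same can be done from assumed rates per infant over six months, with *h* = 0.1 to 0.3 hospitalisations or deaths, *s* = 0.5 to 2 sick visits, and no effect on sick visits. The composite ratio is (0.6*h* + *s*)/(*h* + *s*):
- *h* = 0.3, *s* = 0.5: 0.68/0.80 = 0.85, with *p* = 0.3/0.8 = 0.375.
- *h* = 0.1, *s* = 2: 2.06/2.10 = 0.98, with *p* = 0.1/2.1 = 0.05.

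With no effect on sick visits, the two sets of assumptions together span 0.80 to 0.98. Restricting the count to the Table 2 events returns 0.60.

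**3. Calendar time as a stand-in for age**

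Follow-up is 24 weeks, about 5.52 months. Assume uniform accrual over *L* months and full follow-up. The share of the variance in age explained by calendar time is then 5.52²/(*L*² + 5.52²), with 5.52² = 30.47.

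The accrual dates conflict. Recruitment and retention gives 22 July 2022 to the end of 2023. Trial status gives 22 July 2023 to 31 October 2023.
- *L* = 17.3 (both dates from Recruitment and retention): 30.47/(299.29 + 30.47) = 0.09.
- *L* = 15.3 (the 2022 start with the October 2023 end): 30.47/(234.09 + 30.47) = 0.12.
- *L* = 3.3 (both dates from Trial status): 30.47/(10.89 + 30.47) = 0.74.

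**4. Does it move the treatment comparison?**

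A simulation used 200 trials per setting of 275 infants randomised 1:1. The assumptions were a true rate ratio of 0.60, a control rate of 0.15 per month falling by a factor of exp(−0.35) with each month of age, gamma variation between infants, and 30% loss by 5.5 months. The analysis was a plain Poisson regression with a person-time offset. In the unequal-loss setting the loss hazard was multiplied by 1.6 in the control arm and by 0.4 in the intervention arm, so loss was 1 − 0.7^1.6 = 44% and 1 − 0.7^0.4 = 13%.

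| Loss | Accrual (months) | Unadjusted | Calendar quarter | Month of age |
|---|---|---|---|---|
| equal | 15.3 | 0.589 | 0.591 | 0.589 |
| equal | 17.3 | 0.610 | 0.610 | 0.609 |
| unequal | 15.3 | 0.558 | 0.564 | 0.593 |
| unequal | 17.3 | 0.581 | 0.583 | 0.617 |

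The log rate ratio varied between trials with a standard deviation of about 0.24, so each mean has a Monte Carlo error of about 0.24/√200 = 0.017 on the log scale. The columns within a row come from the same simulated data, so the comparison to make is across a row. With equal loss the adjustments agree. With strongly unequal loss, the calendar term stays next to the unadjusted value and the age term moves away from it.

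**The case against.** Several points on the other side stand.

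- **Poisson model.** A reader might infer that it certainly pools all three event types. The sentence speaks of counts and can mean one count per type. Only the mean cumulative function sentence says composite.
- **Masking.** A reader might infer that an effect on hospitalisation or death would be lost. The Kaplan–Meier and Cox analysis of first hospitalisation or death keeps the Table 2 events, so the question is still answered there.
- **Dominance of clinic visits.** The article gives no rates. That sick visits are much commoner, and that the intervention leaves them unchanged, are both assumptions. The trial's own hypothesis is better infant health, so sick visits may fall too and the dilution would shrink.
- **Reporting bias.** Hospitalisation and death are also first identified by interviewing the mother, and the follow-up interviewer is blinded. The record review makes the contrast one of degree.
- **Calendar time.** It may be loose wording for time since birth. Enrolment is within 24 hours of delivery, so study time is practically infant age. A reader might infer that the adjustment biases the rate ratio, but with equal loss it does not.
- **Remedy.** The authors could instead widen Table 2. That would also mean changing the objective, the hypothesis and the survival analysis, all of which now agree with each other.

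None of this reconciles the mean cumulative function sentence with Table 2. Exploratory status lowers the stakes, but it does not make two event sets into one endpoint.

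**Conclusion.** The concern holds in a limited form. The contradiction is certain for the mean cumulative function and possible for the Poisson model. Followed as written, the Count outcomes section would report a result on a different event set under the name of secondary endpoint 1. How far that result would depart from the stated effect cannot be known from the article. The illustrative range depends on the assumed event shares and on no effect on sick visits. If the sick-visit ratio may lie between 0.9 and 1.1, the table above runs from 0.75 to 1.05.

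The calendar-time point is a mismatch between the adjustment and its stated reason, and it is minor. It would matter for the treatment comparison mainly if follow-up differed between arms. The plan allows for 30% loss and gives weekly contact to one arm only, so this is possible, but the article does not state it. How poor a proxy calendar time is depends on accrual dates on which the article contradicts itself. The claim that the analysis answers a different question rests on the composite alone.

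The primary analysis of exclusive breastfeeding is not touched.

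**What to change.** 1. In Count outcomes, define the composite for both the mean cumulative function and the Poisson model of secondary endpoint 1 as all-cause hospitalisation and death, as in Table 2.
2. Report sick-clinic visits as a separate count and name it as such in Table 2.
3. Replace calendar time with infant age (time since birth), the scale that the survival analysis already uses. Calendar period or season can be added as a further term if it is wanted for its own sake.
4. Reconcile the recruitment dates in Recruitment and retention with those in Trial status.

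The data and the models stay the same; only wording changes. The cost is a composite with fewer events, and so wider intervals, in an analysis already declared exploratory.

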### Safety analyses

Safety data are summarized as count (percent) by study group and in aggregate. When calculating the incidence of safety events, by study group, study visit, and overall, each participant is counted once, and any repetitions are ignored; the denominator is the total sample size.

### Sub-group analyses

Exploratory sub-group analyses are conducted to assess the consistency of intervention effect across potential prognostic factors. Subgroup analyses focus on the evidence for a difference in intervention effects on the primary endpoints: the interaction effect. We present exploratory subgroup-specific summary statistics and use forest plot figures showing possible subgroup effects and interactions.

If the sample size permits, we create the following subgroups and test our hypotheses on the following:Subgroup 1: subdivide the population into two baseline viral load strata—suppressed viral load and high viral loadAnalysis of participants with different follow-up times: complete 1 study visit, 2 study visits, 3 study visits, and all 4 study visits to determine the incremental benefit gained by each additional motivational interview

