### Mobile phone text messaging and motivational interviewing

Every Monday morning, a research assistant sends a text message to mothers in the intervention group, encouraging them to exclusively breastfeed and inquiring if they have any problems with breastfeeding. Mothers are requested to respond by text within 48 h, indicating whether she has a problem with breastfeeding. The research assistant contacts mothers who either indicate a breastfeeding problem or fail to respond within 48 h. Mothers have individual motivational interviews post-delivery at weeks 2, 6, and 10. During the interviews, the research assistant and the mother discuss problems with breastfeeding and potential solutions, reinforce mother’s own self-motivational statements and readiness to change, and affirm the mother’s freedom of choice. Text messaging and motivational interview are discontinued for mothers who completely stop breastfeeding but are followed until the end of the study. As soon as the mother stops breastfeeding completely, the mother-infant pair will have achieved the co-primary outcomes but will still be followed for the secondary outcomes.

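### Grouping participants by number of completed visits cannot show what each additional motivational interview adds, and under no effect it can mislead

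*Protocol article*

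**What the plan says.** The Sub-group analyses section lists an analysis of participants who completed one, two, three or all four visits, with the stated purpose "to determine the incremental benefit gained by each additional motivational interview". It sits beside a subgroup on baseline viral load and is conditional: "If the sample size permits, we create the following subgroups and test our hypotheses on the following". On form, the section says "Subgroup analyses focus on the evidence for a difference in intervention effects on the primary endpoints: the interaction effect", and also "We present exploratory subgroup-specific summary statistics and use forest plot figures showing possible subgroup effects and interactions".

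Three facts from elsewhere in the protocol article bear on this:

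- Interviews (Mobile phone text messaging and motivational interviewing): "Mothers have individual motivational interviews post-delivery at weeks 2, 6, and 10".
- Visits (Recruitment and retention): "four in-person follow-up visits at weeks 2, 6, 10, and 24 post-randomization". Table 1 marks an interview at visits 1 to 3 and none at visit 4.
- Stopping (same section as the interviews): "Text messaging and motivational interview are discontinued for mothers who completely stop breastfeeding but are followed until the end of the study".

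Study procedures and measurements adds that a missed visit is replaced by a telephone interview.

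**The concern.** The stated aim is causal: the benefit of one more interview. The grouping variable is not a baseline prognostic factor. It takes its value after randomisation and may be affected by the assigned arm, so a comparison within or across its levels is no longer protected by randomisation. It also does not count interviews.

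At stake is a statement about how many interviews are worth giving, drawn from groups that cannot support one. The confirmatory test of exclusive breastfeeding does not depend on this analysis.

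**Working it through.** The plan gives no figure for this analysis. Its sample size (182, then 182 × 1.01 = 183.8, so 184, then 184 / 0.67 = 274.6, so 275) concerns the confirmatory comparison and is not in question.

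**1. Does visit count measure interview dose?**

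| Step | Interviews added, intervention arm | Interviews added, usual care |
|---|---|---|
| Visit 1 (week 2) | 1 if still breastfeeding | 0 |
| Visit 2 (week 6) | 1 if still breastfeeding | 0 |
| Visit 3 (week 10) | 1 if still breastfeeding | 0 |
| Visit 4 (week 24) | 0 | 0 |

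The step from three visits to four adds no interview for anyone. A mother who stops completely at week 4 can complete four visits with one interview. Visit count is therefore not dose.

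**2. Group sizes.** Take 275 / 2 = 137.5 per arm and 30% loss (Sample size section), spread evenly over four visits (assumed). Retention per visit is r = 0.70^(1/4) = 0.9147. The number with exactly j visits is 137.5 × r^j × (1 − r), which gives 10.7, 9.8 and 9.0 for j = 1, 2, 3. All four: 137.5 × 0.70 = 96.25.

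**3. What appears if the intervention does nothing?** From the documents: exclusive breastfeeding 8% at week 24, here in both arms; visits at weeks 2, 6, 10 and 24. Assumed: any breastfeeding at week 24 of q = 30%, 50% or 70%; constant stopping hazard, so S(t) = q^(t/24); dropout permanent; attendance probability a while breastfeeding and b after stopping; week-24 feeding known for all, for example by telephone.

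For j = 1 to 3, the rate among mothers with exactly j visits is 0.08 × a^j × (1 − a) / P(j visits). For four visits it is 0.08 × a^4 / P(4 visits). P sums over mothers who stop before week 2, in weeks 2–6, 6–10 or 10–24, or not at all.

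*(A) Attendance unrelated to feeding (a = b = 0.915).* The attendance terms cancel: 8% in every group, risk ratio 1.

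*(B) Attendance depends on feeding, equally in both arms (a = 0.94, b = 0.85).* For q = 50% the five stopping classes are 0.0561, 0.1030, 0.0917, 0.2492 and 0.5.

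- P(4) = 0.0561×0.85^4 + 0.1030×0.94×0.85^3 + 0.0917×0.94^2×0.85^2 + 0.2492×0.94^3×0.85 + 0.5×0.94^4 = 0.7136. Rate = 0.08×0.7807/0.7136 = 8.8%.
- P(3) = 0.15×(0.0561×0.85^3 + 0.1030×0.94×0.85^2 + 0.0917×0.94^2×0.85 + 0.2492×0.94^3) + 0.5×0.94^3×0.06 = 0.0820. Rate = 0.08×0.0498/0.0820 = 4.9%.

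| q | 1 visit | 2 visits | 3 visits | 4 visits |
|---|---|---|---|---|
| 30% | 5.9% | 5.3% | 4.3% | 9.2% |
| 50% | 6.5% | 6.0% | 4.9% | 8.8% |
| 70% | 7.1% | 6.8% | 5.7% | 8.4% |

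These are false within-arm differences. Both arms share them, so the between-arm risk ratio is 1 in every group.

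*(C) Dependence in the intervention arm only (a = 0.94, b = 0.80; usual care 0.915 throughout, so 8% in each of its groups).* The same formula with b = 0.80 and q = 50% gives P(4) = 0.6804, rate 0.08×0.7807/0.6804 = 9.2%, and risk ratio 0.0918/0.08 = 1.15. Risk ratios for 1, 2, 3 and 4 visits:

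- q = 30%: 0.64, 0.57, 0.44, 1.24
- q = 50%: 0.74, 0.67, 0.51, 1.15
- q = 70%: 0.84, 0.79, 0.63, 1.08

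This is a false interaction, though not a steady rise per visit.

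**4. Would counting interviews received repair it?** No. Even with attendance unrelated to feeding (0.915), the rate with three interviews is 0.08/S(10). With two it is 0.08×0.085 / [0.085×S(6) + 0.915×(S(6) − S(10))].

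- q = 30%: 0.08/0.6055 = 13.2%, against 0.0068/(0.0629 + 0.1232) = 3.7%
- q = 50%: 0.08/0.7492 = 10.7%, against 0.0068/(0.0715 + 0.0839) = 4.4%
- q = 70%: 0.08/0.8619 = 9.3%, against 0.0068/(0.0777 + 0.0483) = 5.4%

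Among mothers attending all four visits, those with fewer than three interviews show 0%, because stopping is what ended their interviews.

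**The case against.** The strongest defence is that the section centres on the between-arm interaction, not on raw rates by visit count, and that no rule ties visits to feeding, since mothers who stop are still followed. That stands. In scenarios A and B the between-arm contrast is flat under no effect, and no scenario gave a steady rise with each visit. The analysis is also exploratory and conditional on sample size; groups of about 10 per arm may mean it is never run.

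Four stronger readings are tempting, and the documents do not support them.

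- *A false dose-response is certain.* For visit count it needs attendance to depend on feeding, and for the planned interaction it needs that dependence to differ by arm. Both are plausible, but neither is stated.
- *The artefact is 50 to 67 percentage points.* With 30–50% still breastfeeding at week 24, mothers breastfeeding at week 10 reach 0.30^(14/24) = 49.5% to 0.50^(14/24) = 66.7%, against 0% in those who had stopped. The arithmetic is right, but it concerns any breastfeeding grouped by interviews received, which the protocol does not plan.
- *Groups with one to three visits lack the 6-month endpoint by construction.* A mother may miss an earlier visit and attend week 24, or be reached by telephone. Only mothers whose follow-up ended before week 24 and who were not reached lack it.
- *The result would set a number of sessions for the provincial programme.* The Discussion speaks of adapting services if the intervention works and mentions no number of sessions.

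None of this rescues the aim. Where no false pattern appears, the analysis still does not estimate the benefit of an additional interview, and an exploratory label does not change what is estimated.

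**Conclusion.** The point holds as one of target and interpretation. From the protocol's own schedule and stopping rule, visit count is a post-randomisation variable that does not measure interview dose, so the per-interview aim cannot be met. That conclusion needs no assumption.

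The size of any distortion does rest on assumptions: the attendance probabilities, the constant stopping hazard, and any breastfeeding of 30–70% at week 24. On these, it ranges from none (A), through about 3 to 5 percentage points within an arm between three and four visits (B), to risk ratios of 0.44–0.63 with three visits and 1.08–1.24 with four (C), where the truth is 1. The change is worth making, but the primary conclusion of the trial does not depend on it.

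**What to change.** Delete the visit-count grouping and its per-interview aim from the Sub-group analyses section. In its place, report the randomised between-arm comparison at weeks 2, 6, 10 and 24 in all randomised participants, using the repeated-measures model already planned under Missing data, where the protocol intends to examine how the effect changes over the 24 weeks. This describes the timing of the effect of the whole package, not of a single interview. Any table by visits attended or interviews received should be labelled descriptive and non-causal.

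A complier-average estimate is not a substitute. Randomisation also assigns the weekly text messages, which can affect feeding directly, so the exclusion restriction fails for interview receipt.

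The cost is wording in the protocol or analysis plan. Table 1 already schedules the feeding questionnaire at all four visits. The trial would then make no per-interview dose statement, which its design cannot support in any case.
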